### Interventions

Eligibility work-up will include a complete blood count, serum chemistries, PSA, and radiographic studies (of involved sites) and bone scan. Subjects who meet eligibility criteria and qualify for enrollment will be stratified and randomized (Fig. 1).

**Fig. 1 Fig1:**
[figure not shown]
ORIOLE Study Schema. Subjects who meet eligibility criteria and qualify for enrollment will be stratified and randomized as demonstrated

The following is a detailed outline, after randomization, involving each study arm:Observation Arm: Active Clinical Surveillance
Defined with 3 time points, involving the following:

Day 1Standard blood tests [complete blood count with differential (CBC w/Diff), lactate dehydrogenase (LDH), serum chemistry, and PSA evaluation]Research laboratory tests: CAPP-Seq, rectal swab, and Color Test

Day 90Physician examination, medical history, medication review, performance status, quality of life (QoL) and adverse event (AE) evaluationsStandard blood tests (CBC w/Diff, LDH, serum chemistry, testosterone, and PSA evaluation)Research blood tests: CAPP-Seq

Day 180Physician examination, medical history, medication review, performance status, QoL and AE evaluationsStandard blood tests (CBC w/Diff, LDH, serum chemistry, testosterone and PSA evaluation),Research blood tests: CAPP-SeqImaging: bone scan and CT/MRI
2.SABR Arm:
Defined with 3 time points, involving the following:Day 1Standard blood tests (CBC w/Diff, LDH, serum chemistry, and PSA evaluation)Research laboratory tests: EPIC HD-CTC, ImmunoSEQ, CAPP-Seq, rectal swab, and Color TestImaging: ^18^F-DCFPyL PET/CT or PET/MRI
Day 90Physician examination, medical history, medication review, performance status, QoL and AE evaluationsStandard blood tests (CBC w/Diff, LDH, serum chemistry, testosterone, and PSA evaluation)Research blood tests: ImmunoSEQ, CAPP-Seq
Day 180Physician examination, medical history, medication review, performance status, QoL and AE evaluationsStandard blood tests (CBC w/Diff, LDH, serum chemistry, testosterone, and PSA evaluation)Research blood tests: EPIC HD-CTC, CAPP-SeqImaging: Bone scan and ^8^F-DCFPyL PET/CT or PET/MRI
Research Imaging
^18^F-DCFPyL PET/CT or PET/MRI images will be evaluated and compared to bone scan. However, additional sites(s) of suspected metastatic disease detected using ^18^F-DCFPyL will not be considered for treatment by SABR or undergo further evaluation. The results of PSMA-targeted PET imaging will not be made available to the treating physicians until after the trial is completed and these results will not be made available to the patient.SBRT/SABR Planning and Dosage:
CT- and/or MRI-simulation will be performed with fabrication of a radiation therapy immobilization device custom-made for each patient. The treating radiation oncologist will identify the location of the tumor. Gross tumor volume (GTV) delineation will be performed with a diagnostic radiologist on sequential axial computed tomography images. A radiosurgical treatment plan will then be developed based on tumor geometry and location. The clinical tumor volume (CTV) will equal the GTV. The dose will be prescribed to the minimal isodose line that completely covers the planning target volume (PTV), defined as CTV plus a variable (up to 5 mm) margin. Adjacent normal structures, including but not limited to the heart, esophagus, aorta, spinal cord, kidneys, rectum, bowel, liver, and stomach, within 5 cm of the CTV will be identified for the purpose of limiting incidental radiation to these structures.In addition, prior to treatment delivery, a four-dimensional cone beam CT study will be performed on individual patients to assess respiration and determine targeting accuracy for tumors that may be subject to respiratory motion such as those in the bones of the thorax. If tumor motion is greater than 5 mm, the PTV will be expanded accordingly.SABR will be delivered in 1 to 5 fractions, and the dose and fractionation schedule will depend on the size and location of the lesion and the surrounding normal tissue constraints in accordance with AAPM Task Group 101 recommendations [36].Within three weeks of the initial treatment planning imaging study, SABR will be administered using image-guidance. During treatment, real time cone beam CT images of the patient’s body site of interest will be obtained. Cone beam CT will be obtained immediately prior to treatment and will be repeated until the treatment shift, required to align the planning CT and the cone beam CT performed on the day of treatment, is within tolerance for the body site.
d.Early Stopping Guidelines
Site-specific grade 4/5 toxicity will be monitored in the SABR arm. If it becomes evident that the proportion of grade 4/5 toxicity at specific sites convincingly exceeds 20%, the study will be halted for a safety consultation. Specifically, we will apply a Bayesian toxicity monitoring rule that suspends the enrollment for a posterior probability ≥ 75% of toxicity being larger than 20%. The monitoring rule uses Beta (0.5, 5.5) as prior distribution, meaning our prior guess of the proportion of toxicity is 8.3% with a 90% chance that this proportion is 0.04%-30.6%.

Follow-Up:Patients will be followed from Day 1 to Day 180.All AEs and serious adverse events (SAEs) are recorded on source documents. The investigator will follow up on all AEs and SAEs until the events have subsided, returned to baseline or, in case of permanent impairment, until the condition stabilizes.

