#### Secondary endpoints

To describe the toxicity of SBRT/SABR delivered for the population enrolled using Common Terminology Criteria for Adverse Events (CTCAE) version 4.0.To determine local control at 6-months after SABR in patients with oligometastatic disease.To assess progression free survival (PFS) and ADT-free survival (ADT-FS) after randomization defined as the time interval between the day of randomization and progression.To assess quality of life in the SBRT/SABR arm using the Brief Pain Inventory form [34].To estimate the proportion of ^18^F-DCFPyL-PET/MRI or –PET/CT positive sites that are positive for new or progressive metastatic disease by bone scan/CT at baseline and 6 months following SABR and vice versa.To enumerate CTCs using EPIC HD-CTC platforms at baseline and day 180 from randomization.To enumerate circulating tumor DNA (ctDNA) using Cancer Personalized Profiling by deep sequencing (CAPP-Seq) at baseline, day 90 and day 180 from randomization for control and SABR arms.To quantitatively sequence T-cell receptor (TCR) repertoires using peripheral blood monocytes and the ImmunoSEQ platform at baseline and day 90 from randomization.

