### Evaluation of randomization and blinding

This study will employ a randomized phase II design to determine the appropriateness of a subsequent phase III trial based on comparison of rate of progression at 6 months. An interactive web response system (IWRS) will be utilized to obtain the patient’s randomization assignment. Randomization will occur in a 2:1 fashion for SABR and observation arms, respectively. A minimization approach [35] will be applied to ensure balanced assignment to each treatment arm by: 1) Initial treatment with surgery vs. radiation therapy; 2) Prior hormonal therapy vs. no prior hormonal therapy; and 3) PSADT <6 mos vs. 6-14.9 mos. The on-study date for protocol entry will be the day that the study subject is randomized. Patients will be re-evaluated for radiographic response 6 months after randomization. Trial radiologists evaluating for treatment responses will be blinded to the treatment group and treatment specifics. The trial radiologists and the principal investigator will be unblinded only if a patient progresses at any time during the study.

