#### Data analysis

##### 2.4.2.1.Analysis of primary objective

A minimization approach [35] will be applied to ensure balanced assignment to each treatment arm by: 1) Initial treatment with surgery vs. radiation therapy; 2) Prior hormonal therapy vs. no prior hormonal therapy; and 3) PSADT <6 mos vs. 6-14.9 mos. Baseline PSA level is defined as that measured Day 1 following randomization.The primary clinical outcome will be the proportion of patients who have progressed after 6 months from randomization. For each arm, we will calculate the proportion of patients who have progressed and extract 95% confidence intervals. If a patient has withdrawn from the study before 6 months, they will be considered to have progressed.Progression will be a composite endpoint defined from the Prostate Cancer Working Group 2 (PCWG2) criteria for mCRPC [38] and our previous trials in a population of men with biochemical failure without metastases [37–39]. Progression will be defined as either: 1) a ≥ 25% increase in PSA from nadir (and by ≥ 2 ng/mL), requiring confirmation ≥ 4 weeks later (PCWG2 criteria); and/or, 2) clinical/radiographic-progression defined as symptomatic progression (worsening disease-related symptoms or new cancer-related complications), or radiologic progression (on CT scan: ≥ 20% enlargement in sum diameter of soft-tissue target lesions [RECIST 1.1 criteria]; on bone scan: ≥ 1 new bone lesions), initiation of ADT or death due to any cause, whichever occurs first. Death is considered a severe adverse event here.We will compare the proportion of patients who have progressed in the observation and SABR arms using Fisher’s exact test. The analysis population includes all randomized subjects based on intention-to-treat.

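### The Day 180 schedule lists conventional CT/MRI only for the observation arm, in conflict with the CT-based soft-tissue component of the primary endpoint and with the document's own PET and local-control objectives

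*Protocol article*

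**What the plan says.** The arm-by-arm outline under Interventions (following Fig. 1) gives three time points per arm. At Day 180, observation has a bone scan and CT/MRI. The SABR line reads "Bone scan and ^8^F-DCFPyL PET/CT or PET/MRI". No conventional CT/MRI is listed for SABR at Day 1, 90 or 180.

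The Research Imaging paragraph of the same outline says the PET "images will be evaluated and compared to bone scan", and that "The results of PSMA-targeted PET imaging will not be made available to the treating physicians until after the trial is completed". The patient does not receive them either.

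Analysis of primary objective states "Progression will be a composite endpoint defined from the Prostate Cancer Working Group 2 (PCWG2) criteria for mCRPC". Its radiologic part is "on CT scan: ≥ 20% enlargement in sum diameter of soft-tissue target lesions [RECIST 1.1 criteria]; on bone scan: ≥ 1 new bone lesions". The other components are PSA, symptomatic progression, start of ADT and death.

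Secondary endpoints include the proportion of PET-positive sites that are "positive for new or progressive metastatic disease by bone scan/CT at baseline and 6 months following SABR", and the reverse. The last paragraph of the Background likewise compares PET with conventional bone scan and CT, both for finding lesions before SABR and for monitoring after it.

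Analysis of secondary objectives judges each lesion for local control by RECIST 1.1 or by bone-scan criteria.

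Evaluation of randomization and blinding says "Patients will be re-evaluated for radiographic response 6 months after randomization", for all patients, and "Trial radiologists evaluating for treatment responses will be blinded to the treatment group and treatment specifics".

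**The concern.** The inclusion criteria admit soft-tissue metastases, so the CT criterion can decide whether a patient counts as a progressor. As scheduled, the scan that would normally trigger it is assigned to one arm. In the SABR arm the only listed cross-sectional imaging is a research PET study with restricted results. The document does not say that its CT or MR part is measured for RECIST.

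A soft-tissue progression that meets no other component by 6 months could then be counted under observation and missed under SABR. That error runs in one direction and lowers the counted SABR rate without any treatment effect. The trial has 54 patients and its 6-month comparison is meant to inform a phase III decision, so a few such cases would matter.

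There is also a risk to blinding. If the radiologists received the studies as scheduled, the type of scan could reveal the arm.

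**Working it through.** **Passages side by side**

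| Component of progression | Observation, Day 180 | SABR, Day 180 |
|---|---|---|
| Soft-tissue enlargement on CT | CT/MRI listed | Only the research PET/CT or PET/MRI listed |
| New lesion on bone scan | Bone scan | Bone scan |
| PSA, symptoms, ADT start, death | Same rules and visits | Same rules and visits |

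Only the first row differs. On that row the outline disagrees with the Background and Secondary endpoints, which presume CT alongside bone scan after SABR. Bone lesions can be judged for local control from the bone scan that both arms have. Soft-tissue lesions cannot, unless the CT/MR part of the PET study is used or a CT outside the list exists.

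**Reproducing the plan's figure**

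Inputs from Sample size and accrual: 18 observation and 36 SABR patients, progression 80% versus 40%, one-sided Fisher's exact test at 0.05.

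Let x and y be the progressors in the observation and SABR arms. The one-sided p-value is P(H ≥ x), where H is the number of progressors falling among the 18 when x + y progressors are spread at random over all 54 patients (hypergeometric). The rejection probability is the sum of Bin(x; 18, p_obs) × Bin(y; 36, p_SABR) over all (x, y) with p-value ≤ 0.05.

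With p_obs = 0.80 and p_SABR = 0.40 this gives 85.06%, against the stated 85%. The figure reproduces and is not in dispute.

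**Illustration of unequal ascertainment**

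This rests on an assumption that is not in the documents. True progression is p in both arms, and d percentage points of SABR progressions go uncounted because only a CT would have shown them. Put p_obs = p and p_SABR = p − d into the same sum. The entries are the chance of falsely declaring SABR better.

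| p | d = 0 | 1 | 3 | 5 | 10 | 15 points |
|---|---|---|---|---|---|---|
| 0.50 | 2.95% | 3.44% | 4.63% | 6.15% | 11.75% | 20.47% |
| 0.60 | 2.95% | 3.46% | 4.68% | 6.21% | 11.59% | 19.65% |
| 0.70 | 2.70% | 3.21% | 4.46% | 6.03% | 11.74% | 20.35% |
| 0.80 | 2.13% | 2.62% | 3.87% | 5.54% | 11.87% | 21.41% |

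In SABR patients, 3 points is 36 × 0.03 = 1.1, 5 points is 1.8, 10 points is 3.6 and 15 points is 5.4.

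The loss can also be put as a share of SABR progressors. At p = 0.80, missing 5% gives a counted rate of 0.80 × 0.95 = 0.76 and a false-positive rate of 4.7%. Missing 10% gives 0.80 × 0.90 = 0.72 and 9.0%.

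**The case against.** The best reply is that the outline is not exhaustive. It lists no imaging at Day 90, yet Analysis of secondary objectives starts local-control assessment at three months and refers to a second radiologic reassessment. The Background and Secondary endpoints point to CT after SABR, and all patients are to be re-evaluated radiographically at 6 months. An omission in one line of a condensed article is therefore a plausible reading. This stands as an account of intent. It does not remove the problem, because the article prints both Day 180 lists and they differ on an endpoint scan, so the text needs correcting under either reading.

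Other limits also stand:

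- PET/CT and PET/MRI contain a CT or MR component. The restriction concerns PET results and names treating physicians and patients, not the trial radiologists. A reader might infer that SABR patients have no usable cross-sectional imaging, but the documents do not establish that.
- A reader might infer that the blinded radiologists can tell the arm. No section says which images they receive, so this is a risk and not a stated fact.
- A reader might infer that radiologic progression as a whole is measured differently. Bone scan is listed in both arms, and the CT criterion concerns soft-tissue lesions only. Some patients with soft-tissue enlargement would also count by PSA.
- A reader might infer that local control and the PET comparison cannot be computed under SABR. That is wrong for bone lesions, which may be judged by bone scan, and for the comparison of PET with bone scan.
- The miss rates have no basis in the documents. Up to 3 points missed leaves the false-positive rate below the nominal 5%.

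**Conclusion.** The concern holds in a narrow form. The Day 180 outline conflicts with the primary-endpoint definition, the PET objective and its background rationale, and, for soft-tissue lesions, the local-control assessment. If followed as written, it permits unequal ascertainment of one component of the primary composite, in SABR's favour.

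The size cannot be determined from the document. It depends on how many SABR patients would progress on soft-tissue CT alone by 6 months, and on whether the CT/MR part of the PET study is read. Under assumed losses of 5, 10 and 15 points, with a common true rate of 50-80%, the false-positive rate is about 6%, 12% and 20-21%, against 2-3% with equal ascertainment. These figures show sensitivity and are not an estimate for this trial.

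The stated sample size and power are unaffected. Whether the readers are effectively blinded is left open by the text.

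**What to change.** Reconcile the Day 180 outline with the Background, Secondary endpoints, Evaluation of randomization and blinding, and both Data analysis subsections.

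1. List the same conventional endpoint imaging for both arms at Day 180: bone scan plus CT/MRI of involved sites. Alternatively, state that the CT or MR component of the SABR-arm PET study is read for RECIST without the PET data.
2. Base radiologic progression only on that common set.
3. State that the blinded radiologists receive only those images, with PET data and modality labels removed.
4. Make the comparator in the Research Imaging paragraph agree with the PET objective (bone scan alone, or bone scan/CT).

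The cost is a text correction and at most one conventional CT/MRI per SABR patient, which the PET objective already presumes. If the CT/MR component is used, no scan is added. The total of 54 patients and the 85% power do not change.

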#### Inclusion criteria

Patient must have 1-3 asypmtomatic metastatic tumor(s) of the bone or soft tissue developed within the past 6-months that are ≤ 5.0 cm or < 250 cm^3.^
Patient must have had their primary tumor treated with surgery and/or radiation and salvage radiation to the prostate bed or pelvis is allowed.Histologic confirmation of malignancy (primary or metastatic tumor).Prostate specific antigen (PSA) ≥ 0.5 ng/mL but ≤ 50 ng/mL and Testosterone ≥ 125 ng/dL.PSA doubling time (PSADT) < 15 months. PSADT will be calculated using as many PSA values that are available from time of relapse (PSA > 0.2 ng/dL).Patient may have had prior systemic therapy and/or ADT associated with treatment of their primary prostate cancer. Patient may have had ADT associated with salvage radiation therapy.Patient must be ≥ 18 years of age, have the ability to understand, and the willingness to sign, a written informed consent document.Patient must have an Eastern Cooperative Oncology Group performance status ≤ 2.Patient must have normal organ and marrow function as defined as:Leukocytes >2,000/μL, absolute neutrophil count >1,000/μL, platelets >50,000/μL

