### Stastical analysis

#### Sample size and accrual

The primary endpoint will be progression of disease at 6 months. Historical data on this patient population indicate that >80% would show progression, within a 6-month period without treatment, and thus this is the progression rate we expect in subjects in the control/observation arm [37–39]. We hypothesize that SABR will reduce progression at 6 months by 50% [40]. A sample size using a 2:1 randomization scheme of 36 in the SABR arm and 18 patients in the control group will provide 85% power to detect a decrease in relapse rate from 80% to 40% with a type I error = 0.05 using one-sided Fisher’s exact test. Thus, we will accrue a total of 54 patients. Patients withdrawing within one month of enrollment or prior to day 1 of SABR or observation will be replaced.

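### The only stated toxicity halting rule works site by site, so grade 4/5 events spread across sites in the SABR arm are never added up

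*Protocol article*

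**What the plan says.** The rule is in the protocol article under Interventions, item d, Early Stopping Guidelines. It opens with the unit of monitoring: "Site-specific grade 4/5 toxicity will be monitored in the SABR arm". The condition in words is that if "the proportion of grade 4/5 toxicity at specific sites convincingly exceeds 20%, the study will be halted for a safety consultation". The operational form follows: a rule that "suspends the enrollment for a posterior probability ≥ 75% of toxicity being larger than 20" per cent. On the prior: "The monitoring rule uses Beta (0.5, 5.5) as prior distribution", glossed as "our prior guess of the proportion of toxicity is 8.3% with a 90% chance that this proportion is 0.04%-30.6" per cent.

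The number of patients comes from Sample size and accrual: "36 in the SABR arm and 18 patients in the control group will provide 85% power". The article does not list the sites or say how many patients each is expected to hold. It states no counterpart of the rule for the arm as a whole.

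**The concern.** The SABR arm has only 36 patients. If they are divided by anatomic site, each site may hold few, and the prior carries the weight of 0.5 + 5.5 = 6 patients. In a site of six or fewer, the prior counts for at least as much as the data. A moderate excess present at every site can then stay below the boundary at each one, although the same events counted together would cross it clearly. Followed as written, the rule has no step at which they are counted together. What is at stake is how sensitive the only stated toxicity halt is to a general excess of severe toxicity.

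**Working it through.** **Inputs.** From Early Stopping Guidelines: prior Beta(0.5, 5.5), reference rate 20%, cut-off 75%. From Sample size and accrual: 36 SABR patients. Assumed, because the article does not give them: k equal sites, one site per patient, the same true rate at every site, and a look after every patient.

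**The plan's own figures.** Prior mean = 0.5/(0.5 + 5.5) = 8.33%. The 5th and 95th percentiles are 0.037% and 30.57%. The stated 8.3% and 0.04% to 30.6% reproduce.

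**Boundary.** After x events in n patients the posterior is Beta(0.5 + x, 5.5 + n − x). The rule triggers if P(p > 0.20) ≥ 0.75. The smallest x that triggers is:

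| Patients | 1–2 | 3–5 | 6–10 | 11–14 | 15–18 | 19–23 | 24–27 | 28–32 | 33–36 |
|---|---|---|---|---|---|---|---|---|---|
| Events needed | none possible | 3 | 4 | 5 | 6 | 7 | 8 | 9 | 10 |

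For example, 3 of 6 gives 0.742 (no halt) and 4 of 6 gives 0.906 (halt).

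**Largest arm-level count without a halt.** For k equal sites this is k × (boundary − 1):

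- pooled: 1 × 9 = 9 (25%)
- 2 sites of 18: 2 × 5 = 10 (28%)
- 3 sites of 12: 3 × 4 = 12 (33%)
- 4 sites of 9: 4 × 3 = 12 (33%)
- 6 sites of 6: 6 × 3 = 18 (50%)

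With the least favourable unequal split, 2, 3, 4 and 5 sites allow 11, 13, 14 and 16, so at least six sites are needed to reach 18. Pooled, 18 of 36 has a posterior of 0.9998.

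**Chance of a halt.** Let h be the exact chance that one site triggers. A trigger at any site halts the study, so the study-level chance is 1 − (1 − h)^k. At a true 30%:

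- 2 sites: h = 0.555, 1 − 0.445² = 80%
- 3 sites: h = 0.395, 1 − 0.605³ = 78%
- 4 sites: h = 0.302, 1 − 0.698⁴ = 76%
- 6 sites: h = 0.163, 1 − 0.837⁶ = 66%
- 9 sites: h = 0.084, 1 − 0.916⁹ = 54%

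The pooled rule alone gives 78%.

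**Site-specific rule plus the same rule pooled.** The site-only figures are exact. The combined figures come from 200,000 simulated trials per row, with patients from the sites arriving in random order.

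| Sites | True 30%: site only → both | True 20%: site only → both | True 10%: site only → both |
|---|---|---|---|
| 2 | 80% → 84% | 38% → 43% | 4.5% → 5.6% |
| 3 | 78% → 85% | 38% → 45% | 5.3% → 6.7% |
| 4 | 76% → 85% | 36% → 45% | 5.4% → 6.9% |
| 6 | 66% → 84% | 30% → 43% | 5.0% → 6.8% |
| 9 | 54% → 82% | 22% → 40% | 3.3% → 5.5% |

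**The case against.** **Site-specific monitoring is a reasoned choice.** Under SABR planning the article says that "the dose and fractionation schedule will depend on the size and location of the lesion", so toxicity may well differ by location, and a purely pooled rule could dilute an excess at one site. This stands, and it is why the site-specific look should stay. It does not explain why nothing covers the arm as a whole.

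**The number of sites is unknown and may be small.** Inclusion criteria speak only of "metastatic tumor(s) of the bone or soft tissue developed within the past 6-months", and each patient may have one to three such lesions. One patient can therefore count at several sites, which makes sites larger than assumed here. This stands too. With two or three sites, the site-only rule does about as well at a true 30% as a single pooled rule, and the loss is material only from about four sites upward.

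**An article condenses the full protocol.** Site definitions and a boundary table may be there, and their absence alone is no finding. The point rests on what the article does print: a complete rule whose unit is the site. The operational sentence speaks of toxicity without qualification and could be read as arm-level, but it elaborates the site-level sentence before it. If the arm was meant, the wording needs the same clarification.

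**Stronger readings that the documents do not support.** A reader might infer that half the SABR arm could plausibly suffer grade 4/5 toxicity without a halt. That needs at least six sites with one site per patient. In the six-by-six case the third event must also fall in the sixth patient at every site, because 3 of 3, 3 of 4 and 3 of 5 all trigger. At a true 50% the chance of that pattern is (10/64)⁶, about 1 in 69,000, and six sites would halt 98.4% of the time anyway. A reader might also blame site-by-site monitoring for the absence of a halt at 2 events in 2 patients (posterior 0.736). That result comes from the prior and the cut-off. Pooling gives the same value, so it is no part of this point.

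**Conclusion.** The point holds in a limited form. The arithmetic of the stated rule is correct. The weakness is its unit: it is site-specific, the sites are not listed, and no step adds events across the arm. Its sensitivity to a general excess therefore depends on a number the article does not fix. At a uniform true 30% the halt chance runs from about 80% (2 sites) to 54% (9 sites), and the tolerated arm-level count runs from 9/36 pooled to 12/36 with three or four sites. The 18/36 ceiling with six sites is an unlikely extreme.

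These figures rest on equal sites, one site per patient, a common true rate and a look after each patient. Multi-lesion patients would change them, mostly by making sites larger. The direction does not depend on the exact split: adding the pooled look raised the halt chance at a true 30% for every number of sites tried. The change should be made, but this is a gap in coverage and not an error in the plan's calculations.

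**What to change.** Leave the prior, the 20% reference rate, the 75% cut-off and the site-specific look as they are. Add one sentence applying the same rule also to all SABR patients pooled, and name the sites to which the site-specific look applies. The boundary table above could be printed beside it, so that those reviewing safety can see what each look can detect.

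The editorial cost is a sentence or two and a short table. The statistical cost is about 1 to 2.3 percentage points more false halts at a true 10%. At a true rate exactly equal to the 20% reference the rise is larger, from about 5 points with two sites to about 18 with nine. The sponsor should accept this knowingly, since the consequence is a suspension of enrolment for a safety consultation.
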